### Outcome measures

#### Primary outcome measures

1. **CTC vs barium enema**. Detection rates and diagnostic sensitivity of significant colonic neoplasia by each test

2. **CTC vs colonoscopy**. Requirement for additional tests needed to diagnose or exclude significant neoplasia.

Significant colorectal neoplasia is defined as cancer or polyps 1 cm or larger. Such polyps may have a clinical consequence for patients even if they are not the cause of symptoms. We do not focus on detection rates in the colonoscopy sub-trial because available evidence suggests that colonoscopy and CT have equivalent sensitivity for significant colorectal neoplasia.

#### Secondary outcome measures

• Time to diagnosis or exclusion of cancer for each diagnostic pathway. Time to diagnosis of pathology, if any, responsible for the presenting symptoms.

• Frequency and nature of any adverse events split by diagnostic pathway.

• Technical adequacy for the different diagnostic procedures; need for repeat procedures.

• Psychological reactions, adverse events, and preferences for each diagnostic test. The precise outcomes to be measured have been determined by a qualitative pilot study. Interactions with collected demographic data (e.g. age, gender, socio-economic status) and procedures (e.g. number of procedures) will be assessed.

• Economic costs associated with different investigative trajectories. Patient specific records of costs and outcomes including the influence of conversion to other tests and multiple investigations. Cost utility models to compare management plans with outcome cost will be defined. Test characteristics for CTC and patient preferences/quality of life measures will be combined with the economic evaluation in order to determine overall cost utility.

• Modelling: A generic model will be developed to determine total effectiveness for each diagnostic pathway, populated by outcomes from the trial data so that the findings can be extrapolated beyond the trial. The model will pay particular attention to the incidence, relevance, psychological reaction to, and costs of incidental extra-colonic lesions detected by CTC.

### Sample size

The initial sample size was calculated using the following assumptions:

• Randomisation will be 2:1 in favour of the default diagnostic test (i.e. colonoscopy or barium enema).

• The prevalence of significant colorectal neoplasia (i.e. cancer or polyps 1 cm or larger) in symptomatic adults is approximately 15%.

• In each diagnostic pathway, additional examinations will inevitably be required to diagnose or exclude cancer in some patients. We assumed that the proportions requiring further examinations are respectively 14% for colonoscopy (based on anticipated completion rates), 20% for CTC (based on equivocal findings needing further investigation, the need for polypectomy or biopsy in those patients with neoplasia, and also those with significant extracolonic findings needing further investigation), and 15% for barium enema (based on need for further investigation in those with polyps, false positive findings, and incomplete examination in an elderly group, e.g due to incontinence).

#### 1. Diagnostic yield: CTC vs barium enema

The original sample size assumed a detection rate of significant neoplasia of 15% for CTC and 10% for barium enema. With a 2:1 randomisation in favour of barium enema and an alpha of 0.05 (two-tailed), 2160 patients gave us 90% power to detect a difference in detection rates. A revised sample size was needed once the trial was progressing as the above assumptions were found to be overestimates (see Discussion). The revised sample size assumed a detection rate of 7.5% for CTC and 5% for barium enema. To achieve 80% power to detect a difference in detection rates with 2:1 randomisation in favour of barium enema and an alpha of 0.05 (two-tailed), 3402 patients were needed.

#### 2. Subsequent colonic investigations: CTC vs colonoscopy

The available literature suggests that CTC and colonoscopy are equivalent for diagnosis of cancer. A prevalence of significant abnormality of only 15% means that a trial at least ten times larger would be required to detect a diagnostic difference with reasonable power. In any event, because such differences are likely to be small, the role of CTC will instead turn on organisational factors, economic costs, and on the personal reactions of patients. The number of patients who need further investigations before a diagnosis is made or refuted is central to this; the "conversion rate". All the interventions tested will sometimes incur other tests, because of technical failure for example, but the conversion rate is likely to be highest with CTC because more structures are visualised than with colonoscopy or barium enema.

Conversion rates of 20% for CTC and 14% for colonoscopy were assumed. Assuming 2:1 randomisation in favour of colonoscopy and an alpha of 0.05 (two-tailed), an original sample size of 2160 provided 90% power to detect a difference in conversion rates. As the trial progressed, it became apparent that recruitment to this sub-trial was lower than anticipated. Power was lowered to the more conventional 80% and retaining other assumptions as above, the revised sample size was 1430.

Power calculations for psychological outcomes were based on the Short form of the State Trait Anxiety Scale (STAI). 4320 patients randomised overall (see sections above) gave considerable overall power. However, our findings need to be particularised to different settings and subgroups so that the modelling exercise is accurate. We therefore need adequate power in the smallest important patient group – i.e. those needing further investigations following CTC, including those with a positive diagnosis of cancer (i.e. 20% of 720 + 720 = 288). This is sufficient to give us 90% power to detect an 0.5 s.d. difference in STAI scores whose mean value is 10.1 (s.d. 3.5), allowing for a 20% questionnaire non-completion rate.

### Analysis

The two sub-trials will be analysed as two separate case-control studies. In each sub-trial, cases and controls will be compared regarding covariates, including age, sex and centre, using chi-squared or Fisher's exact test for categorical variables and an unpaired t-test for continuous variables. The primary outcomes will be analysed using multivariable logistic regression with study group as the primary explanatory variable and adjustment for other covariates, including age, sex and centre. Centre will be considered as a random variable and the analysis will be clustered on centre. Secondary outcomes will be analysed using poisson regression for counts and logistic regression for proportions with the same explanatory variables. The data will be analysed in Stata 9.2 and variables will be considered significant at the 5% level.

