Interested centres were also asked to perform a "sham-randomisation" exercise both to prove that they could identify potential patients in sufficient numbers, and to focus their attention on how this might be achieved. Over a two-month period each centre was asked to identify patients who satisfied trial inclusion criteria, record simple demographics for them (age, sex, symptoms, referral route, and whole-colon investigation requested), and to enter these on a secure, password-protected web-based database. No patients were approached directly but this "sham-randomisation" provided an evidence-based estimate of how each centre might perform in reality, once the trial was running. 25 centres registered for the sham randomisation and the 10 best-performing were ultimately selected (four of these had already been identified as pilot sites because of extensive pre-existing familiarity with CTC). We believe this procedure restricted participation to those centres most likely to recruit well in practice and identified others in advance who would probably fare poorly, thereby avoiding resource wastage. For example, some centres who registered for the sham-randomisation ultimately failed to register a single patient.

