One centre withdrew in 2005 following the recommendation of the Data Monitoring Committee. At the same time a decision was made to extend recruitment to other centres in order to accelerate recruitment (see Appendix). Increasing the number of centres was feasible because trial procedures and materials had already been developed and piloted, rolled-out, and were running efficiently at most centres. Also, the marginal cost of a new centre was low versus the cost of the trial as a whole. The decision to implement new centres was taken only when effective recruitment was established at existing centres; new centres would be very unlikely to enhance a trial that is failing to recruit at existing centres. It is also vital to keep existing centres motivated and ensure that the data are forthcoming. We have exerted considerable effort on retrieving completed data forms from centres.

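### Centre is given three roles in the primary model without saying how they combine; depending on the reading and the number of centres, tests at a nominal 5% run at about 5% to 11%

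*Protocol article*

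**What the plan says.** All of the model specification is in the Analysis section of the protocol article. The primary outcomes are to be analysed by multivariable logistic regression on study group, with "adjustment for other covariates, including age, sex and centre". The next sentence reads "Centre will be considered as a random variable and the analysis will be clustered on centre". Secondary outcomes reuse these explanatory variables in Poisson or logistic models. The significance rule is that "variables will be considered significant at the 5% level", which matches the two-sided 0.05 in the sample-size sections. The two sub-trials are analysed separately.

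The software statement, "The data will be analysed in Stata 9.2", does not settle the estimator. The section names no variance estimator, small-sample correction or reference distribution.

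On the number of centres, the Discussion says that of 25 that registered for the sham randomisation, "the 10 best-performing were ultimately selected". Later, "One centre withdrew in 2005 following the recommendation of the Data Monitoring Committee", and at the same time "a decision was made to extend recruitment to other centres in order to accelerate recruitment". How many were added is not in the text available. The Randomisation section describes individual patients allocated 2:1 in favour of the default test.

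**The concern.** The three roles are not interchangeable. If centre enters as fixed indicators, a random centre intercept has almost nothing left to explain. If centre is a random intercept, it should not also be a fixed covariate. If clustering is a separate instruction, the natural reading is a variance estimated from between-centre variation in the score contributions, and that behaves differently from a random intercept when centres are few.

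Two things are at stake. First, different readings give different standard errors and p-values from the same data, for both primary outcomes and for the secondary models, so the choice could be made after results are seen. Second, a cluster-robust variance based on about ten centres and compared with 1.96 tends to be too small. On that reading the confidence intervals are too narrow and the false-positive rate exceeds the stated 5%.

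**Working it through.** **Inputs from the protocol article.** Barium enema sub-trial: 7.5% against 5%, 80% power, N = 3402. Colonoscopy sub-trial: 20% against 14%, 80% power, N = 1430. Both use 2:1 allocation and two-sided 0.05. Ten initial centres, one withdrawn, an unstated number added.

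**Assumed, not in the documents.** G between 9 and 20 centres; standard deviation of centre log-odds 0.3; centre sizes equal or unequal (Dirichlet shares, parameter 3); 2:1 allocation held within each centre; no treatment-by-centre variation; age and sex omitted.

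**Step 1: reproduce the plan's own figure.** With d the difference in proportions, r = 2 and p̄ = (p₁ + 2p₂)/3, the smaller arm needs n = [1.960·√(1.5·p̄(1−p̄)) + 0.842·√(p₁q₁ + p₂q₂/2)]²/d².

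- Barium enema: p̄ = 0.0583, so n = (0.5626 + 0.2568)²/0.025² ≈ 1074.4, which rounds up to 1075 (total 3225). The continuity correction, (n/4)·[1 + √(1 + 6/(2nd))]² applied to the unrounded n, gives 1134, and 3 × 1134 = 3402. This matches "2:1 randomisation in favour of barium enema and an alpha of 0.05 (two-tailed), 3402 patients were needed".
- Colonoscopy: the same formulas give 452 (total 1356), and 477 with the correction (total 1431, against 1430 stated).

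The sample sizes are therefore reproduced by a calculation on independent patients, with no allowance for clustering.

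**Step 2: closed form on the cluster-robust reading.** The variance is A⁻¹·[G/(G−1)·Σ s_g s_g′]·A⁻¹, where A is the information matrix and s_g is the summed score in centre g. With G similar centres the test statistic behaves roughly like t on G−1 degrees of freedom, so comparing it with 1.96 gives a true level of P(|t_{G−1}| > 1.96).

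**Step 3: null simulation.** There were 4000 runs per scenario, with event rates of 5% (N = 3402) and 14% (N = 1430). The ranges cover equal and unequal centres, with and without centre indicators.

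| G | Closed form | Robust z, barium enema | Robust z, colonoscopy | Robust t (G−1), both | Model-based, both |
|---|---|---|---|---|---|
| 9 | 8.6% | 8.9–10.3% | 8.5–10.9% | 5.1–6.6% | 4.5–6.1% |
| 10 | 8.2% | 8.4–9.6% | 8.5–9.6% | 4.8–6.2% | 4.6–5.1% |
| 15 | 7.0% | 6.7–8.3% | 6.7–7.7% | 4.3–6.2% | 4.4–5.0% |
| 20 | 6.5% | 6.5–7.3% | 6.5–6.9% | 5.0–5.8% | 4.6–5.7% |

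The Monte Carlo standard error is about √(0.09 × 0.91/4000) = 0.45 percentage points at a 9% level.

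A separate simulation used 1500 runs, unequal centres and event rates of 5.5% and 15%. For G = 9, 10, 15 and 20 the robust z test rejected in 10.1%, 7.8%, 7.3% and 6.7% of barium enema runs and in 10.3%, 8.9%, 8.5% and 8.7% of colonoscopy runs.

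**Step 4: random-intercept reading.** A likelihood-ratio test in a random-intercept logistic model (1500 runs, unequal centres) rejected in 5.4% of runs (barium enema) and 3.8% (colonoscopy) with 10 centres, and in 5.0% and 5.3% with 20. There is no inflation.

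**The case against.** The strongest reply is that the two sentences can be read as one model. The first lists what is adjusted for; the second says how centre enters, as a random effect with centre as the grouping unit. That is a random-intercept logistic model, and Step 4 shows that it holds its level. The article nowhere writes robust or sandwich. Even on the cluster-robust reading, the excess comes from pairing a few-cluster variance with a normal reference. That pairing is not stated, and a journal article may leave it to the full plan.

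This stands as far as it goes. A reader might infer that the primary tests do run at 8–10% and are invalid. The document does not support that: it depends on one reading of one clause, an unstated reference distribution and the initial number of centres, which later changed. What remains is more than missing detail. The article chose to specify how centre is handled, and if the last clause is to add anything to the random effect, a natural way to carry it out exceeds 5%.

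A second objection is also partly right. It is tempting to say that individual randomisation within centres makes any centre-level variance unnecessary. That holds only if the treatment effect is the same in every centre, which both sets of simulations assume. The CT colonography section leaves contrast, spasmolytic, software, reading mode and diagnostic thresholds to local choice, so the effect could vary.

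A rough calculation shows the scale. With equal centres and 5.5% events, the variance of the log odds ratio is about 4.5/(3402 × 0.055 × 0.945) = 0.0254. Variation in effect with standard deviation τ adds τ²/G when the target is the average effect across centres. For G = 10, model-based errors then run at about 5.5% (τ = 0.1), 6.8% (τ = 0.2) and 9.2% (τ = 0.3); for G = 20, at about 5.2%, 5.9% and 7.1%. The colonoscopy figures are nearly the same. The values of τ are assumptions. Keeping clustered errors is therefore defensible if they have a suitable reference distribution.

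**Conclusion.** The point holds in conditional form. The handling of centre is ambiguous, and the ambiguity matters for both primary outcomes. A cluster-robust variance with a normal reference gives a true level of about 8–11% with 9–10 centres and about 6–9% with 15–20; a random intercept gives about 5%. The excess on the first reading persists over the whole range of G examined and shrinks as centres are added.

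These figures rest on the assumptions listed in the working, chiefly a centre standard deviation of 0.3 on the logit scale, a common treatment effect and an unknown final number of centres. They do not show that the trial's tests are invalid, only that the text permits an analysis that would not keep its stated level. The article reports the trial as in a position to close, so the choice should be settled before the data are analysed.

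**What to change.** State one model for each primary outcome: logistic regression with a random intercept for centre, fixed effects for allocated arm, age and sex, and model-based standard errors. Remove centre from the list of fixed covariates and delete the clustering clause.

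If the sponsor wants to allow for treatment-by-centre variation and therefore keeps clustered errors, say so and refer them to a t distribution with G−1 degrees of freedom, where G is the number of centres contributing to that sub-trial. Carry the same choice into the secondary logistic and Poisson models.

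The cost is a short edit to the Analysis section and somewhat wider intervals than uncorrected clustered errors would give. For the t option, the multiplier rises from 1.960 to 2.262 with 10 centres (2.262/1.960 = 1.15, about 15% wider on the log-odds scale) and to 2.093 with 20 (about 7% wider). The model-based option carries the assumption of a common treatment effect across centres, which should be stated.

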Around 363,000 cases of colorectal cancer occur each year in the European Union and 148,000 in the USA [10]. It is important to make an early diagnosis because prognosis depends on tumour stage but local variations in clinical practice can delay this [11]. English patients with symptoms suggestive of colorectal cancer must be now be seen by a specialist within 2-weeks of referral by their general practitioner [12]. A "whole-colon" test is frequently requested to search for cancer but because the "suggestive symptoms" are non-specific and common in the general population (e.g. abdominal pain, change in bowel habit), most patients investigated do not have the disease. Colonoscopy is the most sensitive test but is expensive, resource intensive, technically difficult, and has a small but well-recognised morbidity and even mortality [13]. Furthermore, most patients investigated are elderly, the group most at risk from adverse events. Barium enema is safer than colonoscopy [14] but has reduced sensitivity [15], and interpretation skills are declining [16]. CTC is safer than colonoscopy [17,18] while being more sensitive than barium enema, and appears to be more acceptable to patients than either of the other tests [8]. CTC may also be performed by technicians and in principle the data could be read by computer-assistance [19], accelerating diagnosis and throughput.

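### For rare serious adverse events, the single covariate-adjusted model set for all secondary outcomes may give no finite estimate or usable Wald interval, and no sparse-data method is named

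*Protocol article*

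**What the plan says.** The Secondary outcome measures section of the protocol article lists "Frequency and nature of any adverse events split by diagnostic pathway". No severity threshold is attached, and no rate is given there or elsewhere.

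The Analysis section sets the method for all such outcomes in one sentence: "Secondary outcomes will be analysed using poisson regression for counts and logistic regression for proportions with the same explanatory variables". The variables carried over are those of the primary model, described as "multivariable logistic regression with study group as the primary explanatory variable and adjustment for other covariates, including age, sex and centre". It adds: "Centre will be considered as a random variable and the analysis will be clustered on centre".

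An exact test is mentioned once, for another purpose: "cases and controls will be compared regarding covariates, including age, sex and centre, using chi-squared or Fisher's exact test for categorical variables".

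On how common harm is, the Background says that colonoscopy "has a small but well-recognised morbidity and even mortality". It places both comparators below colonoscopy: "CTC is safer than colonoscopy" and "Barium enema is safer than colonoscopy".

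**The concern.** Adverse-event frequency is a count or a proportion, so the Analysis sentence covers it whichever way it is expressed. That sentence makes no exception for sparse data. The article's own description suggests that the serious end of the outcome will be sparse: harm on colonoscopy is called small, and harm on CTC is said to be lower. The 2:1 allocation also gives CTC, the test described as safer, the smaller arm in the colonoscopy sub-trial.

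If one arm has no events, the maximum-likelihood log odds ratio (or log rate ratio under Poisson regression) is infinite. Software then prints an arbitrary large coefficient with a huge standard error. Even with an event in each arm, a handful of events cannot support terms for study group, age and sex plus a centre variance over ten or more centres.

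Relative safety is part of the case for CTC in the Abstract and Background, and physical morbidity is a study objective. Followed literally, the plan could yield a serious-event contrast that cannot be interpreted, or lead to a method being chosen after the data are seen.

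**Working it through.** **Arm sizes.** The revised totals in the Sample size section are 3402 (barium enema sub-trial) and 1430 (colonoscopy sub-trial), at 2:1 in favour of the default test. Both were reproduced with the usual two-proportion formula (pooled variance under the null, two-sided 0.05, 80% power, ratio k = 2) and the continuity correction n′ = (n/4)·[1 + √(1 + 2(k+1)/(n·k·|d|))]², where n is the CTC arm and d the difference:

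- 7.5% v 5%: n = 1075 uncorrected, 1134 corrected; total 3 × 1134 = 3402 (stated 3402).
- 20% v 14%: n = 452 uncorrected, 477 corrected; total 3 × 477 = 1431 (stated 1430).

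The arms are therefore 1134 CTC and 2268 barium enema, and about 477 CTC and 953 colonoscopy.

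**Chance of an empty arm.** With risk a on CTC (n₁ patients) and b on the default test (n₂), P(no CTC events) = (1−a)^n₁ and P(no default-test events) = (1−b)^n₂. P(at least one empty arm) is the sum of the two minus their product. All rates below are assumptions, because the article gives none.

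Colonoscopy sub-trial (477/953):

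| Risk CTC / colonoscopy | Expected events, total | P(CTC empty) | P(colonoscopy empty) | P(at least one empty) |
|---|---|---|---|---|
| 0.05% / 0.1% | 1.2 | 0.788 | 0.385 | 87% |
| 0.05% / 0.2% | 2.1 | 0.788 | 0.148 | 82% |
| 0.1% / 0.3% | 3.3 | 0.620 | 0.057 | 64% |
| 0.1% / 0.5% | 5.2 | 0.620 | 0.008 | 62% |
| 0.2% / 0.5% | 5.7 | 0.385 | 0.008 | 39% |
| 0.3% / 0.3% | 4.3 | 0.239 | 0.057 | 28% |
| 0.5% / 0.5% | 7.2 | 0.092 | 0.008 | 10% |
| 1% / 1% | 14.3 | 0.008 | <0.001 | 0.8% |
| 2% / 2% | 28.6 | <0.0001 | <0.0001 | <0.01% |

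Barium enema sub-trial (1134/2268), same risk in both arms: 71% at 0.05%, 39% at 0.1%, 11% at 0.2%, 0.3% at 0.5%.

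**What the model does with an empty arm.** Take 0/477 v 3/953, with simulated age and sex as covariates. The log odds ratio for study group runs from −5.7 to −15.7 to −20.7 as the iteration limit rises from 10 to 20 to 30. Its standard error runs from 8.9 to 1315 to about 16,000. There is no finite estimate to converge to.

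A larger split shows the mechanism more starkly. For 0/477 v 10/953, unadjusted logistic regression gives a coefficient of about −22, a standard error of about 16,300 and a Wald p of 0.999. Fisher's exact p is 0.036. Poisson regression fails in the same way.

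**What a sparse-data method gives.** For 0/477 v 3/953, the exact two-sided 95% upper limit on CTC is 1 − 0.025^(1/477) = 0.77%, and Fisher's p is 0.56. For the risk difference, the Wilson (score) limits are 0 to 0.799% for 0/477 and 0.107% to 0.921% for 3/953, whose observed risk is 0.315%. Combining them by Newcombe's method, CTC minus colonoscopy, in percentage points:

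- lower: −0.315 − √(0² + (0.921−0.315)²) = −0.92
- upper: −0.315 + √(0.799² + (0.315−0.107)²) = +0.51

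This is a finite, readable interval from the same data.

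**The case against.** - **The outcome is any adverse event, not serious events.** This stands. The article names no separate serious-event or mortality contrast. A composite that includes minor events need not be sparse: at 2% the 477-patient arm expects 477 × 0.02 = 9.5 events and an empty arm is practically impossible. A reader might infer that the whole adverse-event analysis fails; the documents do not support that.
- **The rate is assumed.** This also stands. An empty arm is likely only at low rates. The Background says small without a figure, so whether it would happen often cannot be settled from the article.
- **A test still exists.** A reader might infer that the stated model allows no valid inference at all. That goes too far. The article names a model family, not Wald inference, and a likelihood-ratio test and a one-sided profile limit can be computed. They are poor approximations at these counts: for 0/477 v 10/953 the unadjusted likelihood-ratio p is 0.004 against Fisher's 0.036.
- **Significance is not rescued.** A reader might infer from 0 v 10 that the plan would miss real differences that Fisher's test would find. That split implies 10/953 = 1.05% on colonoscopy, above the low-rate scenarios. At 0.5% on colonoscopy and 0.05–0.1% on CTC, ten or more colonoscopy events with none on CTC has a probability of only 1.5–1.9%. With few events Fisher's test is not significant either: 0/477 v 5/953 gives p = 0.18, and at least nine colonoscopy events are needed against an empty CTC arm.
- **A fallback belongs in the full analysis plan.** This would answer a complaint that detail is missing. Here, however, the article does not leave the method open: it assigns one to every secondary count and proportion, and keeps the exact test for covariates. If the full plan already has a sparse-event rule, the two texts only need to be aligned.

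**Conclusion.** The point holds in a limited form. The Analysis section commits every secondary count or proportion to one adjusted model with random centre. For rare serious adverse events or deaths, that model may give no finite estimate and no usable Wald interval or test.

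On assumed rates, an empty arm is more likely than not in the colonoscopy sub-trial when the CTC risk is 0.1% or less, and in the barium enema sub-trial at about 0.05% in both arms. In the colonoscopy sub-trial the chance falls to 10% at 0.5% in both arms and vanishes at 2%. Even without an empty arm, one to five events are too few for the stated covariates and a centre variance.

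The primary outcomes and sample sizes are untouched, and so is a common any-event composite. What is at stake is whether the serious-harm contrast can be reported with a valid interval, not whether it reaches significance.

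**What to change.** Add a rule to the Analysis section. It should apply to serious adverse events, deaths and any adverse-event category with an empty arm or with fewer events than a minimum stated in advance. For these, report the number and percentage by randomised pathway, the risk difference with an exact or score 95% confidence interval, and Fisher's exact test (or a Firth-penalised model). Keep the adjusted Poisson or logistic regression for categories with enough events.

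This takes a sentence or two and needs no new data. The cost is that the simple rare-event comparison is not adjusted for age, sex and centre. Randomisation makes that acceptable, and so few events could not support the adjustment anyway.
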